**13. Methods of Statistical Analysis**

| All events were measured from the date of randomization. OS was defined as the time from the date of radiotherapy to death or the latest date known to be alive. Durations were calculated from the end of treatment. The Kaplan-Meier method was used to calculate the actuarial rates of local control, DFS and OS. The χ2 test was used to compare incidence rates and categorical variables and Student’s t-test was used to compare the means of continuous variables, designated to be significant at p<0.05. |
| --- |

**14. Potential Risk Arising from Study**

| 14.1 | Induce discomfort or distress | Yes |
| --- | --- | --- |
| 14.2 | More invasive than the usual management | No﹡ |
| 14.3 | Increase physical or psychological risk | No |
| 14.4 | Involve a potential toxin, mutagen or teratogen | No |
| 14.5 | Involve radiation or radioactive substance | Yes |
| 14.6 | Incur other hazards | No |
| 14.7 | If yes to any of the above, provide details: | |
| Item 14.1.The most common acute toxicities were mucositis, with 52.4% to 54.6% grade 2 toxicity and 28.6%~31.8% grade 3 toxicity. Late toxicities were grade 1-2 skin dystrophy, subcutaneous fibrosis, xerostomia, and hearing loss. No patient had grade 4 late toxicity.  Item 14.5. Radiation therapy itself involves radiation. The use of 18F-FDG-PET/CT may slight impact on the surrounding environment, especially in the patient's excreta. | |
| 14.8 | Significant difference(s) from usual management: | |
|  | PET/CT-guided dose escalation radiotherapy is well-tolerated for patients with locally advanced NPC as compared to conventional chemoradiotherapy. | |

**15. Anticipated Benefits to Study Subjects**

| PET-CT fusion may have significant impact on staging and radiotherapy treatment delineation in NPC. PET/CT-guided dose escalation radiotherapy appears to be well-tolerated. The SMART-IMRT technique to enhance BED of GTV, combined with concurrent chemotherapy, is completely feasible for local advanced NPC. |
| --- |

**16. Research Subject Protection**

| 16.1 | Will subjects be provided with a card indicating their participation in study and means of urgent contact? | Yes |
| --- | --- | --- |
| 16.2 | Does protocol state compliance with the Declaration of Helsinki?  (http://www.wma.net/e/ethicsunit/helsinki.htm) | Yes |
| 16.3 | Does protocol state compliance with ICH-GCP? | Yes |

**17. Information and Consent**

| 17.1 | In what form will consent be obtained? | | | | | Written |
| --- | --- | --- | --- | --- | --- | --- |
| 17.1.1 | State reasons if not written or applying to waive the consent requirement | | | | | |
|  | | | | | |
| 17.2 | Will an interpreter be available when required? | | | | | Yes |
| 17.3 | In obtaining informed consent from subjects, what is the minimal time given to a subject to consider after explanation has been given? | | | | | |
| 3 Day(s) | | | | | |
| 17.4 | Who will carry out the informed consent process? | | | | | |
| × | Principal investigator | × | Co-investigators | | |
|  | Research assistant |  | Others, specify: |  | |
| 17.5 | If subjects are incompetent in giving consent, to whom will the study be explained? | | | | | |
| Principal investigator | | | | | |

**18. Data and Safety Monitoring**

| 18.1 | Will an independent committee review data and safety of study? | | Yes local﹡ |
| --- | --- | --- | --- |
| 18.2 | If yes, who funds this committee? | Hospital and principal investigator | |
| 18.3 | Composition | Principal investigator | |

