**PART Ⅱ: STUDY DETAILS**

**9.** Scientific basis

| 9.1 | Background, current evidence and key references: | | |
| --- | --- | --- | --- |
|  | Nasopharyngeal carcinoma (NPC) differs from other head and neck malignancies in terms of its epidemiology, pathology, and treatment outcomes. It is endemic in China and is one of the major public health problems. Concurrent radiotherapy and chemotherapy is the primary treatment for patients with NPC. In recent years, with the development and application of comprehensive treatment and Intensity Modulated Radiation Therapy (IMRT) technology, the overall prognosis of nasopharyngeal carcinoma has been significantly improved, 5-year survival rate was 74.5% , 3 -year local control rate was 90%[2]. Despite such aggressive treatment, many patients with locally advanced NPC still develop locally recurrent disease [3].Since local control is directly related to patient’s morbidity and mortality in NPC, there is a strong requirement to develop a method for improving current treatments’ efficacy.  One strategy to improve local control is escalating the dose of radiotherapy. This is because local control has been shown to be directly related to the radiotherapy dose . Several techniques, including brachytherapy , stereotactic radiosurgery , and dose-painting intensity modulated radiotherapy (IMRT) , have been used to increase radiotherapy dose. However, due to the large number of critical anatomic structures near the nasopharynx, dose-escalation in NPC can also lead to increased toxicities . One of the more effective techniques is the simultaneous modulated accelerated radiation therapy (SMART) IMRT technique [10]. It delivers both accelerated radiotherapy and hypofractionated radiotherapy to the GTV. The main challenge for these treatments is to identify the appropriate tumor volume that could be received the high-dose radiotherapy. Conventional dose-escalation is conducted via using computed tomography (CT) to identify the gross tumor volume (GTV). However, recent progress in the field of ﬂuorine-18-ﬂuorode-oxyglucose positron emission tomography/computed tomography (18F-FDG-PET/CT)-adjuvant treatment planning allows more accurate tumor volume delineation ]. Thus, we hypothesize that of 18F-FDG-PET/CT-adjuvant treatment planning can improve dose-escalation radiotherapy for NPC, which in turn can improve therapeutic efficacy as well as reducing toxicity.  To identify this hypothesis, we compared the efficacy and toxicity of three treatments, including conventional chemoradiotherapy, CT-guided dose-escalation chemoradiotherapy and PET/CT guided dose-escalation chemoradiotherapy, in patients with locally advanced NPC via a randomized clinical trial in our department. PET-CT fusion may have significant impact on staging and radiotherapy treatment delineation in NPC. PET/CT-guided dose escalation radiotherapy appears to be well-tolerated. The SMART-IMRT technique to enhance BED of GTV, combined with concurrent chemotherapy, is completely feasible for local advanced NPC.  [1] Wei WI, Sham JS. Nasopharyngeal carcinoma. Lancet. Jun 11-17 2005;365(9476):2 041-2054.  [2] Lu H, Peng L, Yuan X, Hao Y, et al.Concurrent chemoradiotherapy in locally advanced nasopharyngeal carcinoma: a treatment paradigm also applicable to patients in Southeast Asia. Cancer Treat Rev. 2009, 35 (4):345-353.  [3] Wee J, Tan EH, Tai BC, et al. Randomized trial of radiotherapy versus concurrent chemoradiotherapy followed by adjuvant chemotherapy in patients with American Joint Committee on Cancer/International Union against cancer stage III and IV nasopharyngeal cancer of the endemic variety. J Clin Oncol. 2005;23(27):6730-6738.  [4] Marks JE, Bedwinek JM, Lee F, Purdy JA, Perez CA. Dose-response analysis for nasopharyngeal carcinoma: an historical perspective. Cancer. Sep 15 1982;50(6):1042-1050.  [5] Teo PM, Leung SF, Tung SY, et al. Dose-response relationship of nasopharyngeal carcinoma above conventional tumoricidal level: a study by the Hong Kong nasopharyngeal carcinoma study group (HKNPCSG). Radiotherapy and oncology : journal of the European Society for Therapeutic Radiology and Oncology. Apr 2006;79(1):27-33.  [6] Teo PM, Leung SF, Lee WY, Zee B. Intracavitary brachytherapy significantly enhances local control of early T-stage nasopharyngeal carcinoma: the existence of a dose-tumor-control relationship above conventional tumoricidal dose. International journal of radiation oncology, biology, physics. Jan 15 2000;46(2):445-458.  [7] Hara W, Loo BW, Jr., Goffinet DR, et al. Excellent local control with stereotactic radiotherapy boost after external beam radiotherapy in patients with nasopharyngeal carcinoma. International journal of radiation oncology, biology, physics. Jun 1 2008;71(2):393-400.  [8] Lin S, Pan J, Han L, et al. Nasopharyngeal carcinoma treated with reduced-volume intensity-modulated radiation therapy: report on the 3-year outcome of a prospective series. Int J Radiat Oncol Biol Phys. 2009; 75(4):1071-8.  [9] Ashamalla H, Guirgius A, Bieniek E, et al. The impact of positron emission tomography/computed tomography in edge delineation of gross tumor volume for head and neck cancers [J]. Int J Radiat Oncol Biol Phy, 2007, 68 (2):388-395.  [10] Butler EB, Teh BS, Grant WH, 3rd, et al. Smart (simultaneous modulated accelerated radiation therapy) boost: a new accelerated fractionation schedule for the treatment of head and neck cancer with intensity modulated radiotherapy. International journal of radiation oncology, biology, physics. Aug 1 1999;45(1):21-32.  [11] Madani I, Duthoy W, Derie C, et al. Positron emission tomography-guided, focal-dose escalation using intensity-modulated radiotherapy for head and neck cancer. International journal of radiation oncology, biology, physics. May 1 2007;68(1):126-135.  . | | |

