**11. Risk Assessment whether Expedited Review is Suitable**

| 11.1 | Will study incur extra clinical intervention(s) to subjects? | | | | NO |
| --- | --- | --- | --- | --- | --- |
| 11.2 | Will study impose additional risk to subjects? | | | | NO |
| 11.3 | Will study raise sensitive / important privacy concerns? | | | | NO |
| 11.4 | Will the study involve the following vulnerable subjects? | | | |  |
| 11.4.1 | - Foetuses in Uteri/ non-viable foetuses / abortus | | | | NO |
| 11.4.2 | - Infants (age 0 to ＜1) | | | | NO |
| 11.4.3 | - Children (age 1 to ＜13) | | | | NO |
| 11.4.4 | - Adolescents (age 13 to ＜18) | | | | NO |
| 11.4.5 | - Pregnant / lactating women | | | | NO |
| 11.4.6 | - Persons related unequally to investigators, e.g. student, employee | | | | NO |
| 11.4.7 | - Special population, e.g. prisoner, mentally / cognitively disabled | | | | NO |
| 11.4.8 | - Others: | NO | Specify if yes: |  | |
| 11.5 | Are there any special precautions to protect the interest of vulnerable subjects? | | | | |
|  | In the course of treatment, when patients with adverse reactions, it will get timely medical assistance. According to the patient informed consent, waive part of medical expenses. | | | | |

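### The safety committee declared independent has the principal investigator as its only listed member, and the no-added-risk answers conflict with the protocol's own account of dose escalation

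*Protocol*

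**What the plan says.** **Oversight (Protocol, section 18).** The form has three entries on safety oversight. Item 18.1 asks "Will an independent committee review data and safety of study" and is answered yes, at local level. Item 18.2 reads "If yes, who funds this committee? | Hospital and principal investigator". Item 18.3 reads "Composition | Principal investigator", with no other member and no sign of redaction.

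**Risk (Protocol, sections 11 and 14).** Section 11 is the assessment of whether expedited review is suitable. Item 11.1 answers No to extra clinical intervention, and item 11.2 reads "Will study impose additional risk to subjects? | | | | NO". In section 14, item 14.3 ("Increase physical or psychological risk") is also answered No. The same section answers Yes to discomfort or distress (14.1) and to radiation (14.5), and 14.7 lists acute and late toxicities.

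**Design (Protocol, sections 8, 9 and 12).** Section 9.1 says that "dose-escalation in NPC can also lead to increased toxicities", because critical structures lie close to the nasopharynx. Item 12.3 lists 77 Gy for the PET/CT-guided arm and 70 Gy for control. Section 8 treats the FDG-PET/CT as an ethical matter needing separate waiting, separate disposal of excreta, isolation and a radiation check. Short-term and long-term toxicity are secondary outcomes (9.5).

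**The concern.** There are two separate inconsistencies, and neither depends on the other.

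The first concerns the safeguard itself. Independent review is meant to put accumulating safety data before someone with no stake in the result. The form tells the ethics committee that this will happen, then fills the seat with the person who leads the trial. If harm from the escalated arm began to show, the only listed reviewer would be the person with the strongest reason to continue. The risk is late recognition of harm and conduct influenced by knowledge of the data.

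The second concerns what the ethics committee is told about risk. Whether escalation adds toxicity is one of the questions the trial sets out to study, and two form items answer it in advance with No. One of those items sits in the section that informs the choice of review route.

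**Working it through.** No sample size, power or event count is involved, so the check is a comparison of entries, with one line of arithmetic.

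**Step 1: independence.**

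| Item | Entry | Consequence |
|---|---|---|
| 18.1 | Independent committee: yes, local | Claims independence |
| 18.2 | Funded by the hospital and the principal investigator | The investigator has a financial role in the committee |
| 18.3 | Composition: principal investigator | One listed member, who leads the trial |

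Independent members listed: 1 member − 1 investigator = 0. The answer at 18.1 cannot be true with the entry at 18.3. The composition field gives a role, not a removed name, so this is not an effect of how the text was prepared. The protocol does not leave the matter to another document either: it answers the question, then contradicts its answer.

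**Step 2: risk.**

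| Answered No | Text that conflicts |
|---|---|
| 11.2, additional risk | 9.1: escalation can raise toxicity; 12.3: higher listed dose in the PET/CT arm |
| 14.3, increased physical or psychological risk | The same, plus 14.1, 14.5 and 14.7 |
| 11.1, extra clinical intervention | Section 8: FDG-PET/CT with its own precautions |

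Listed dose difference from item 12.3: 77 − 70 = 7 Gy, and 77 / 70 = 1.10. The PET/CT arm is therefore listed at a nominal total dose 10% above control, and 9.1 links escalation to more toxicity. The No answers at 11.2 and 14.3 do not fit that.

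Item 11.1 is the weaker case. The protocol does not say whether PET/CT is already part of usual work-up at the site. The entry needs reconciling with section 8, but the text does not settle which answer is right.

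**Step 3: are the two linked?** No. The lack of independence follows from 18.1 to 18.3 alone and would stand whatever sections 11 and 14 said.

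**The case against.** The strongest case on the other side is that these are form-filling slips, that the protocol is open about harm elsewhere, and that the ethics committee receives the whole form. It can read the doses in 12.3, the toxicity sentence in 9.1 and the Yes answers at 14.1 and 14.5 for itself. Much of this stands: the fault is inconsistency, not concealment. It does not rescue 18.1, because nothing elsewhere in the form supplies an independent member.

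A reader might infer more than the documents support:

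- **That there is no safety oversight at all.** Section 18 does describe review, by the principal investigator. Only its independence is contradicted.
- **That the investigator would examine efficacy by arm during the trial.** Section 18 speaks of data and safety. No interim efficacy look and no review by arm is described.
- **That the toxicity rates in 14.7 measure the problem.** Grade 3 mucositis is put at 28.6% to 31.8%, which for 30 patients would be 0.286 × 30 = 8.6 to 0.318 × 30 = 9.5. The rates are not attributed to the escalated arm or compared with control. They show neither excess harm from escalation nor anything about oversight.
- **That expedited review was obtained on false grounds.** The available text does not show that it was requested or granted. The most one can say is that the choice of route could be affected.
- **That the investigator also controls consent.** Item 17.4 ticks co-investigators as well, and 12.7 has a research nurse obtaining consent. The point needs no support from this.

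**Conclusion.** The point holds in two parts. First, items 18.1 and 18.3 contradict each other: the form declares an independent committee but lists none but the principal investigator, who also co-funds it. The number of independent members is zero, and the stated independence does not exist as written. Second, the No answers at 11.2 and 14.3 conflict with 9.1, 12.3, 14.1, 14.5 and 14.7. Because section 11 informs whether expedited review is suitable, the review route could rest on a wrong premise.

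This should be corrected. It is a defect in subject protection and in what the ethics committee is told, and it does not undermine the planned efficacy analysis. The conclusion assumes that 18.3 is a complete list of the membership. If other members exist, they need to be entered there. It does not assume that escalation causes more harm, only that the protocol says it can. No view is taken on which dose is right.

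**What to change.** 1. **Item 18.3.** Replace the principal investigator with members who have no role in the trial: not investigators, not treating staff, and not drawn from the collaborating parties in 23.2, which share responsibility for the study. The investigator supplies reports to the committee but does not sit on it.
2. **If that cannot be done,** change 18.1 to No. This adds no protection, but it stops the ethics committee being told that independent review exists and lets it decide with that knowledge.
3. **Items 11.2 and 14.3.** Correct them to agree with 9.1, 12.3 and 14.7.
4. **Item 11.1.** Reconcile it with the study PET/CT in section 8, stating whether the scan is usual work-up at the site.

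**Cost.** The form corrections are trivial. The membership change takes some time from colleagues outside the trial, on a committee that 18.1 and 18.2 already declare and fund. The study dates in section 6 run from 2/2009 to 4/2014, so the commitment could span several years. Arms, doses, sample size and endpoints are unchanged.

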**19. Confidentiality and Use of Results**

| 19.1 | How will data be handled and stored during and after completion of the study, and who will be responsible for its safekeeping？ |
| --- | --- |
|  | The research center has a full-time staff for handling and storing data during the study. All data will be sent to archives of ethics committee for safekeeping after completion of the study. |
| 19.2 | Who will have access to the data or study record during or after the study? |
|  | Principal investigator and authorized personnel |
| 19.3 | How long will the data be kept and what will be done with them after completion of storage period? |
|  | 10 years |

**PART Ⅲ：BUDGET AND USE OF RESOURCES**

**20. Source of Funding**

| 20.1 | Commercial source: | No﹡ | Sponsor(if applicable): ﹡ |
| --- | --- | --- | --- |
| Name (1) |  |
| Name (2) |  |
| 20.2 | Non-  commercial source: | Type of funding | Granting body (if applicable): ﹡ |
| Local research grant﹡ | the National Natural Science Foundation of China (No.81071831) |
| Local research grant﹡ | Jiangsu Provincial Health Bureau issues (NO.H201021) |
| Local research grant﹡ | Xuzhou City Science and Technology Bureau issues (NO. XF10C082). |
|  |  |

**21. Resources Implication and Conflict of Interest**

| 21.1 | Will this study use HA resources? | | No﹡ |
| --- | --- | --- | --- |
| 21.1.1 | If yes, provide details: | | |
|  |  | | |
| 21.2 | How will this affect the waiting time of other patients with competing needs? | | |
|  | Potential biases do not affect results of waiting time study | | |
| 21.3 | Will study site (hospital) receive reimbursement for the study? | No﹡ | |
| 21.3.1 | Is there a non-monetary (drug, consumable, equipment or research assistant) sponsorship? | No﹡ | |
| 21.3.2 | If yes, give details: | | |
|  | | |

**22. Financial Costs and Payment to Subjects**

| 22.1 | Will the subjects be charged for the study article/service | No |
| --- | --- | --- |
| 22.2 | Will the study article continue to be available to subjects after study (if subjects benefited from it) until it is commercially available? | No |
| 22.3 | If yes to either 22.1/22.2, how will be the cost be met and by whom? | |
|  | |
| 22.4 | Does the consent form explain the above arrangement? | Yes |
| 22.5 | Will subjects receive payment? | No |
| 22.5.1 | If yes, specify nature, amount and payment schedule: | |
|  | |

**23. Research Organization and Indemnity**

| 23.1 | The organization/individual responsible for securing the arrangements to initiate and/or manage a study: | | |
| --- | --- | --- | --- |
| Department of Radiation Oncology, Affiliated Hospital of Xuzhou Medical College. [name], Professor and MD | | |
| 23.2 | Collaborating parties that jointly take on the responsibilities for the study: | | |
| Collaborating party(1) | Department of Radiation Oncology, University of North Carolina-Chapel Hill, Chapel Hill, NC, USA | |
| Collaborating party(2) | PET-CT Center, Xuzhou Central Hospital, Xuzhou, Jiangsu, China. | |
| Collaborating party(3) |  | |
| 23.3 | If this is an industry sponsored trial, will the sponsor indemnify study related claims? | | N/A﹡ |
|  | If yes, :answer the following | | |
| 23.3.1 | -Is the indemnity agreement based on the HA approved form? | | N/A |
| 23.3.2 | -Will a copy of the agreement be submitted to Cluster REC? | | N/A |
| 23.3.3 | -Will a copy of the insurance policy backing the indemnity be submitted to Cluster REC? | | N/A﹡ |

[figure not shown]
